#### Implementation

The PHC care model and its associated implementation strategies, codesigned and refined during Phase I, will be deployed in the six clusters allocated to the intervention arm. Control clusters will continue to deliver usual care and will be offered the intervention package after the trial if it proves effective. Intervention clusters will participate in a Quality Improvement Learning Network (QILN), a collaborative platform designed to foster shared learning, experimentation and continuous improvement in care delivery and outcomes.^30^ The QILN will be delivered through virtual activities, including quarterly online sessions involving all intervention sites (‘full-house’ meetings), monthly 30 min group outreach sessions focused on emerging implementation challenges, and monthly 1-hour multisite meetings to support peer learning and problem-solving. Sessions will be facilitated by trained study coordinators and local experts and will combine brief structured inputs with facilitated discussion to support experimentation, reflection and exchange of experiences across centres. The QILN is designed to be embedded within existing professional routines and relies on low-cost virtual platforms, facilitating continuation of peer-learning activities beyond the trial period if the intervention proves effective.

#### Outcomes

The primary outcome will be a composite outcome including glycaemic control (HbA1c <8%); blood pressure control (<140/90 mm Hg); and use of statins (statin prescription) limited to patients ≥40 years. The source to obtain this data will be routine clinical records.

Secondary outcomes measured through participant questionnaires include user-reported quality of care (key secondary outcome), PHC engagement, system competence, patient confidence in the health system, inequities in outcomes and patient empowerment. User-reported Quality of Care is the overall rating of quality of care from enrolled patients, categorised as ‘excellent or very good’ versus ‘good’ or worse. PHC engagement is measured as the percentage of visits conducted at the PHC level during the data collection period, with positive engagement defined as ≥75% of all non-urgent ambulatory visits.^31^ System competence is defined as ≥75% of enrolled patients per site adhering to the complete set of selected diabetes prevention recommendations from national and provincial guidelines: annual eye exam, yearly foot exam, annual kidney function assessment, annual blood pressure measurement and biannual HbA1c measurement during the follow-up period. Patient confidence in the health system is measured by the combination of three aspects in the e-Cohort survey: health security, endorsement of the current system and trajectory.^32^ Security: We will calculate the percentage of respondents answering ‘somewhat’ or ‘very confident’ to ‘How confident are you that you would receive good quality healthcare if you became very sick?’ and ‘that you could afford the healthcare you needed if you became very sick?’. Confidence: The proportion of respondents indicates that in the past 2 years, the health system has been improving (vs staying the same or getting worse). Endorsement is indicated by agreement that the system works well and needs only minor reforms (vs significant changes needed or need to be completely rebuilt). To assess inequities, we will explore gender, migration status, education and income as potential variables related to underperformance in primary outcomes. Finally, we will measure patient empowerment using the Diabetes Empowerment Scale. This instrument is free and easy to use and has been adapted and validated in its Spanish version.^33^

Direct costs related to diabetes care: Estimated from costs assessed included medications, diagnostic tests, procedures, medical supplies and visits with health professionals. Results will be reported on average per outpatient visit in USD using Purchasing Power Parity Index from ARS. Source: Accounting Department of Ministry of Health.

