## Methods and analysis

### Aims

The primary objective is to improve disease control in individuals with T2D. Secondary objectives are (a) to improve the care experience, (b) to assess the feasibility and acceptability of the redesigned model and its implementation package, (c) to test the model’s impact on service use patterns, system competence, user confidence and cost per visit and (d) to analyse the impact of the model on potential inequalities by sociodemographic factors.

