### Phase II: trial deployment

#### Setting

The trial will be implemented in PHC centres across the province of Mendoza, Argentina, which serve approximately 45% of the population, primarily individuals from socioeconomically disadvantaged backgrounds. The province is administratively divided into 18 departments. The unit of randomisation (cluster) will be the department. 12 departments will be selected, each contributing at least two PHC centres. Clusters will include two or three PHC centres providing care to ≥50 individuals diagnosed with T2D per cluster. Centres involved in the pilot phase will be excluded from phase II.

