#### Sample size

Based on preliminary data from the diagnostic phase and published literature, the baseline rate of achievement for the composite primary outcome (glycaemic control (HbA1c <8%); blood pressure control (<140/90 mm Hg); and use of statins (statin prescription) -limited to patients ≥40 years-) in the control group is estimated at 30%. The intervention is expected to improve this to ≥50% (absolute effect size of 20%). We have calculated the sample size considering a parallel cluster randomised trial with a cohort design, including baseline and follow-up assessments. The trial is powered at 80% to detect an absolute difference of 20 percentage points between the control group (30%) and the intervention group (50%) on the composite primary outcome, assuming a two-sided significance level of 5%. The design includes six clusters per arm (12 in total) and accounts for the correlation structure of repeated measures using a two-period decay model. Specifically, we assumed an intracluster correlation coefficient (ICC) of 0.05, a cluster autocorrelation of 0.5, and an individual autocorrelation of 0.6. Standard errors were adjusted using a t-distribution to account for the small number of clusters. Based on these parameters, the required sample size before adjusting for attrition is 312 individuals (26 per cluster). Applying an attrition inflation factor of 1.25 (to allow for 20% loss to follow-up), the final sample size increases to 396 individuals (33 per cluster, 198 per arm).

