#### Data analysis

We will use all available data from all randomised clusters and conduct all analyses on the intention-to-treat (ITT) population, including all clusters and patients in the randomised group, regardless of intervention adherence. Summary statistics will be given for baseline data by treatment group using means, SD, medians, minimum, maximum and quartiles for continuous variables and counts and percentages for categorical variables. We will quantify complete vs incomplete records and describe the characteristics of patients lost to follow-up.

For the composite clinical outcome, the primary ITT analysis will compare the proportion of patients achieving an HbA1c level <8%, blood pressure control <140/90 mm Hg and statin uptake between the trial arms at the end of the study. We expect a good covariate balance between the groups; therefore, the ITT analysis will be performed by comparing proportions. Patient and cluster-level covariates can be included in a mixed-effects logistic regression model to account for the cluster effect and obtain an adjusted estimate of the average treatment effect for within-cluster change.^35^ Adjusted ORs will be reported with 95% CIs, p values and ICCs will be reported to estimate the percentage of variance explained by each level.

For quality of care, we will compare the proportion of patients reporting overall quality of care as ‘excellent’ or ‘very good’ before and after the intervention phase between trial arms using difference-in-difference regression analysis to estimate the average treatment effect. Engagement and confidence in the health system will be evaluated by comparing the proportion of patients achieving the expected threshold in each trial using a χ^2^ test for proportions. Fisher’s exact test will evaluate system competence across participating PHC centres. Direct costs related to diabetes care will be reported for each group. We may expect higher costs in the intervention group due to increased and better utilisation of health services. The mean cost will be analysed considering the variable distribution (non-normal/normal). For all outcomes, we will conduct mixed effects regression adjusted for covariates and clustered by department to provide an average treatment effect for expected change in outcomes within each department.

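### System competence is tested as a pass/fail per health centre, which discards the patient-level data and is likely uninformative unless completion of the full set of checks is already high

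*Protocol article*

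**What the plan says.** Under Outcomes, the protocol article gives the definition: "System competence is defined as ≥75% of enrolled patients per site adhering to the complete set of selected diabetes prevention recommendations". The set is "annual eye exam, yearly foot exam, annual kidney function assessment, annual blood pressure measurement and biannual HbA1c measurement during the follow-up period". A patient counts only if all five items are met, and a centre counts only if three quarters of its patients do.

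Under Data analysis, the test is fixed: "Fisher’s exact test will evaluate system competence across participating PHC centres". The same section adds: "For all outcomes, we will conduct mixed effects regression adjusted for covariates and clustered by department". It does not say whether, for system competence, that regression models each patient's completion or each centre's pass/fail.

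Under Setting: "Clusters will include two or three PHC centres providing care to ≥50 individuals diagnosed with T2D per cluster". Sample size gives 12 clusters, six per arm, with 26 patients per cluster before attrition and 33 after. Aims lists the outcome within secondary objective (c): "to test the model’s impact on service use patterns, system competence, user confidence and cost per visit". No section gives a completion rate for the set, at baseline or expected, and no power is claimed for this outcome.

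**The concern.** The outcome is dichotomised twice: all-or-none per patient, then all-or-none per centre at 75%. Any improvement that leaves most centres on the same side of 75% is invisible to the test. A centre going from 20% to 60% of patients fully checked scores the same as one that did not change. The unit tested is then one of 24 to 36 centres, each classified on a handful of patients.

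At stake is the system-competence item of objective (c). If completion starts low, a real and sizeable gain in guideline care could be reported as no difference, although the trial holds the patient-level data that would show it.

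**Working it through.** **Patient counts (Sample size, Setting).** The plan's inflation reproduces: 26 × 1.25 = 32.5, rounded up to 33; 33 × 12 = 396. Its 80% power for the primary outcome is also approximately reproduced (79.4 to 79.7% at 26 per cluster with 20 to 22 degrees of freedom). There is no corresponding figure for system competence.

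- Centres: 12 × 2 = 24 to 12 × 3 = 36, so 12 to 18 per arm.
- Enrolled per centre: 33/3 = 11 to 33/2 = 16.5. After loss: 26/3 = 8.7 to 26/2 = 13.
- Patients needed to reach 75%: 7 of 9, 9 of 11, 10 of 13, 12 of 16.

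**What Fisher's test needs.** With no passing control centre, 4 of 12 intervention centres gives p = 0.093 and 5 of 12 gives p = 0.037. With 18 per arm, 4 gives p = 0.104 and 5 gives p = 0.046. At least five must pass.

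**Assumptions.** The completion rate is not in the document, so a range is shown, each time with a true 20-point gain. The ICC of 0.05 is borrowed from the primary outcome.

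**Centre-level power.** P(pass) is the beta-binomial probability that at least the required number of a centre's patients complete the set. Power is the exact sum, over all pairs of passing counts, of the probability that Fisher's two-sided p is at most 0.05.

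**Patient-level power.** Non-central t with 10 df; SE = √{[p₀(1−p₀) + p₁(1−p₁)] × [1 + (M−1) × 0.05] / (6M)}, with M patients per department. For 30% vs 50% and M = 26: variance sum 0.21 + 0.25 = 0.46; design effect 1 + 25 × 0.05 = 2.25; SE = √(0.46 × 2.25/156) = 0.0815; 0.20/0.0815 = 2.46 against a critical value of 2.228; power 60%. With M = 33 it is 64%.

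| Completion, control vs intervention | Expected passes, 12 centres/arm, 13 patients | Expected passes, 18 centres/arm, 9 patients | Fisher power (9 to 16 patients per centre) | Patient-level power (M = 26 to 33) |
|---|---|---|---|---|
| 20% vs 40% | 0.0 vs 0.4 | 0.1 vs 1.0 | 0 to 0.2% | 66 to 70% |
| 30% vs 50% | 0.1 vs 1.2 | 0.3 vs 2.4 | 0.3 to 7% | 60 to 64% |
| 40% vs 60% | 0.4 vs 2.8 | 1.0 vs 5.0 | 9 to 31% | 58 to 62% |
| 50% vs 70% | 1.2 vs 5.5 | 2.4 vs 8.7 | 34 to 51% | 60 to 64% |
| 60% vs 80% | 2.8 vs 8.6 | 5.0 vs 13.0 | 57 to 72% | 66 to 70% |

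**Sensitivity to the ICC.** At an assumed ICC of 0.20, patient-level power falls to about 27 to 32% throughout. Fisher power is 1 to 5% at 20% vs 40%, 5 to 16% at 30% vs 50%, 13 to 24% at 40% vs 60%, and 21 to 34% at 50% vs 70%. The patient-level advantage remains at low completion and largely disappears above about 40% in the control arm.

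**How demanding 75% is.** Purely as illustration, with five independent checks: 80% on each gives 0.8⁵ = 33% jointly, 90% gives 59%, and 75% jointly needs about 94% on each (0.75^(1/5) = 0.944).

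**The case against.** The strongest reply is that a site benchmark is a legitimate target. System competence is a property of a centre, the 75% cut mirrors the one used for PHC engagement, user-reported quality of care is the key secondary outcome rather than this one, and no power is claimed here. That stands, and it is why the benchmark should be kept as a reported figure.

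A reader might infer that almost no centre can pass and that objective (c) cannot be answered. The document supports neither. Both need a completion rate it never gives, and the 30% assumed for the primary composite cannot be borrowed: that concerns control and statin prescription, whereas these items are checks received. At 60% vs 80%, about 9 of 12 or 13 of 18 intervention centres pass. Objective (c) also has three other items. The Introduction does report deficits in system competence and difficulty obtaining laboratory tests, which makes low or moderate completion a reasonable planning case, but it is not a rate.

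The mixed-effects regression promised for all outcomes is a fair point too. Fitted to patient-level completion, it already answers the concern. Fitted to the centre pass/fail, it inherits the floor. Data analysis leaves this open, and the analysis plan is not shown. The definition and the Fisher test, however, are fixed in the article itself.

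Two limits apply to the calculation. The correlation is placed at centre level for Fisher's test and at department level for the patient comparison, so the two are not strictly like for like. The patient-level comparison is itself below 80% in every case shown.

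**Conclusion.** The point holds as a conditional loss of information. As defined and tested, system competence reduces 396 patient results to 24 to 36 binary values. If intervention-arm completion is about 50% or less, a true 20-point gain would very probably go undetected: Fisher power of about 0 to 7%, against about 60 to 70% for a department-clustered patient-level comparison, assuming an ICC of 0.05. The gap narrows as completion rises and closes at about 60% vs 80%. With an ICC as high as 0.20 it largely closes above about 40% baseline completion.

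One open matter could worsen the floor. The definition counts enrolled patients, and the missing-data text treats missing clinical outcomes as failures and then extends its approach to secondary outcomes. If that rule applies here, with 20% loss and no between-centre correlation, Fisher power at 50% vs 70% is only 0.4 to 0.8% with 16 or 11 enrolled per centre. The wording may equally refer only to the weighting analysis, so the conclusion does not rest on this.

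**What to change.** Under Outcomes, make the tested measure the proportion of enrolled patients who received the complete set during follow-up. Under Data analysis, replace the Fisher sentence for this outcome with the mixed-effects model clustered by department that is already planned, and state that it is fitted to patient-level completion. Report the share of centres reaching 75% by arm as a descriptive benchmark.

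The cost is one definition and one analysis sentence, with no new data. The downside is that the site-level benchmark is no longer the tested quantity.

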**Ethics and dissemination:**

All study activities will comply with national and international ethics guidelines, presenting minimal risk to participants. The protocol was submitted and approved by the local independent ethics committee at the Mendoza Ministry of Health (Consejo Provincial de Evaluación ética en investigación en Salud-Provincial Health Research Ethics Review Board, Reference number: 149/2024). Facility-level permission will be obtained for participation and sharing of deidentified data. Written informed consent will be required from study participants, who will receive information on the study’s purpose, procedures, risks and benefits. Dissemination activities and outputs will include writing and submitting manuscripts for publication; writing policy briefs to support strategy implementation in other regions or countries; and tailoring outputs for patients, clinicians and researchers. We anticipate that improvements in disease management and patient experience will have clinical and economic benefits related to reduced usage of secondary-level and tertiary-level facilities, lower cost per visit and a reduced number of clinical events related to diabetes.

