## Ethics and dissemination

All study activities will comply with national and international ethics guidelines, presenting minimal risk to participants. The protocol was submitted and approved by the local independent ethics committee at the Mendoza Ministry of Health (CoPEIS—Consejo Provincial de Evaluación ética en investigación). Facility-level permission will be obtained for participation and sharing of deidentified data. Written informed consent will be required from study participants (patients with T2D who meet the eligibility criteria), who will receive information on the study’s purpose, procedures, risks and benefits. Evaluation forms, surveys and records will use coded identifiers to ensure confidentiality. Records will be securely stored, and clinical information will only be released with written participant permission or for regulatory monitoring.

Dissemination activities and outputs will include writing and submitting manuscripts for publication; writing policy briefs to support strategy implementation in other regions or countries; and tailoring outputs for patients, clinicians and researchers. We anticipate that improvements in disease management and patient experience will have clinical and economic benefits related to reduced usage of secondary-level and tertiary-level facilities, lower cost per visit and a reduced number of clinical events related to diabetes. On a larger scale, this project constitutes one of the first experiences in SDR for NCDs, and its findings will be informative for future work in this line of research and health policy worldwide with a particular focus on LMICs.

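### The only cost unit defined is cost per outpatient visit, but the intervention is expected to change visits, so cost per visit can fall while cost per patient rises

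*Protocol article*

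**What the plan says.** The protocol article deals with cost in four places.

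- **Aims**, secondary objective (c), is to test the model's "impact on service use patterns, system competence, user confidence and cost per visit". Service use and cost per visit are thus both things the model is meant to affect.
- **Outcomes** describes direct costs: "costs assessed included medications, diagnostic tests, procedures, medical supplies and visits with health professionals". It then fixes the unit: "Results will be reported on average per outpatient visit in USD using Purchasing Power Parity Index from ARS". The source is the accounting department of the Ministry of Health.
- **Data analysis** (Phase III) says: "Direct costs related to diabetes care will be reported for each group". It adds: "We may expect higher costs in the intervention group due to increased and better utilisation of health services". It names the mean cost as the quantity to be analysed, with regard to its distribution, but does not restate the unit. The same paragraph plans covariate-adjusted mixed-effects regression, clustered by department, for every outcome.
- **Ethics and dissemination** (abstract and main text) anticipates clinical and "economic benefits related to reduced usage of secondary-level and tertiary-level facilities", and continues the list with "lower cost per visit and a reduced number of clinical events related to diabetes".

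The Data collection section adds that visit data and costs are extracted for all consenting patients, for the facilities taking part. The cohort is followed for 12 months for outcome assessment.

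**The concern.** A ratio compares two randomised arms fairly only if its denominator is unaffected by allocation, or if the ratio itself is what the decision-maker needs. Neither is secure here. The protocol expects the intervention to raise utilisation and to move care away from secondary and tertiary facilities, so both the number and the mix of visits may differ between arms because of the intervention.

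The numerator also includes items that need not grow in step with visits, such as medication and tests done once or twice a year. Spread over more visits, they lower the cost per visit without any reduction in spending.

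The two stated expectations, higher costs in the intervention arm and a lower cost per visit, can both come true if visits rise. In that case the one cost figure with a defined unit is the favourable one. The results are addressed to provincial policymakers, who need to know what the model costs per patient cared for.

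**Working it through.** The article states no cost estimate, so there is no figure to reproduce. The check asks whether the defined measure can move against cost per patient, and under what conditions.

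**Inputs from the protocol article.** Unit: average per outpatient visit (Outcomes). Expected direction: utilisation and costs up in the intervention arm (Data analysis), and cost per visit down (Ethics and dissemination). Neither is given a size. Nor does the article say how much of the extra utilisation would be outpatient visits. Every number below is therefore assumed.

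**Step 1: identity.** Cost per patient = visits per patient × cost per visit. If visits change by a fraction *a* and cost per visit by *b*, then

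change in cost per patient = (1 + *a*)(1 + *b*) − 1.

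Cost per patient rises whenever cost per visit falls by less than 1 − 1/(1 + *a*).

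| Visits | Break-even fall in cost per visit |
|---|---|
| +10% | 1 − 1/1.10 = 9.1% |
| +25% | 1 − 1/1.25 = 20.0% |
| +50% | 1 − 1/1.50 = 33.3% |

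Examples:
- Visits +25%, cost per visit −10%: 1.25 × 0.90 − 1 = +12.5% per patient.
- Visits +50%, cost per visit −20%: 1.50 × 0.80 − 1 = +20% per patient.
- Visits unchanged, cost per visit −10%: −10% per patient. Here the two measures agree.

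**Step 2: a mechanism with no change in prices.** Let a patient's yearly cost be *F* + *u* × *v*, where *F* is drugs and tests not tied to visits, *u* the cost of a visit and *v* the number of visits. Assume *F* = 300 and *u* = 25.

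| Visits | Cost per patient | Cost per visit |
|---|---|---|
| 4 | 300 + 100 = 400 | 100 |
| 5 | 300 + 125 = 425 (+6.25%) | 85 (−15%) |
| 6 | 300 + 150 = 450 (+12.5%) | 75 (−25%) |

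**Step 3: let the drug and test cost rise.** The trial aims to increase statin prescription and completion of guideline tests, so holding *F* constant is not neutral. Cost per visit is *F*/*v* + *u*. With *u* unchanged it falls only if *F* grows proportionally less than *v*. Take *F* = 60 and *u* = 20:

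- 4 visits, *F* = 60: 60 + 80 = 140 per patient, 35.0 per visit.
- 6 visits, *F* = 60: 60 + 120 = 180 per patient (+29%), 30.0 per visit (−14%).
- 6 visits, *F* = 90: 90 + 120 = 210 per patient (+50%), 35.0 per visit (no change).

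With 50% more visits, then, the signs differ if *F* rises by less than 50%. At 50% the per-visit measure shows nothing while cost per patient is up by half. Above 50% both measures rise.

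**The case against.** The best defence is that the protocol is open about cost. It says in advance that it expects higher costs in the intervention arm, which sits badly with any suggestion that it would hide them. A reader might infer that the plan labels a lower cost per visit a saving. It does not use that word, and it lists cost per visit as one of three things linked to clinical and economic benefits. A lower cost per visit could also reflect a real gain, if care moves from costlier secondary or tertiary settings to primary care without extra visits. This stands: the per-visit measure is not always misleading. But it cannot by itself tell that case from the one in which visits rise.

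A second defence is that the unit is less settled than it seems, because Data analysis speaks of mean cost by group without naming a unit, and service use is an objective beside cost per visit. That is fair, but per visit is the only unit defined anywhere, and no per-patient total is promised.

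A reader might also infer that choosing the method by distribution leads to rank tests, which would not compare mean costs. The text does not support this. It names the mean as the target, mentions no rank test and plans mixed-effects regression for all outcomes. The handling of skewed costs may properly be left to an analysis plan that is not shown.

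Finally, the illustrations rest on assumed inputs, and Step 3 shows that the fall in cost per visit disappears if drug and test costs rise enough. This stands in full and limits what can be claimed about size.

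**Conclusion.** The point holds in a limited form. Cost per outpatient visit is the only cost unit the protocol defines, and its denominator is a post-randomisation quantity that the intervention is expected to change. A between-arm comparison of cost per visit therefore does not estimate the effect on cost per patient and can point the other way.

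The reversal is a possibility, not a forecast. It requires that visits rise and that cost per visit falls by less than the break-even amount (for example 20.0% when visits rise 25%). Whether cost per visit falls at all depends on how far drug and test costs also rise. No size for this trial can be derived from the document. Cost is a secondary outcome, so the primary clinical conclusion is untouched, but the change should be made before results are known.

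**What to change.** 1. In **Outcomes** and **Data analysis**, make mean direct cost per enrolled patient over the fixed 12-month follow-up the main between-arm cost comparison, estimated with the department-clustered mixed-effects regression already planned.
2. Keep cost per visit, which serves the stated objective, and report visits per patient beside it, by level of care where captured, so that the product can be read.
3. In both **Ethics and dissemination** texts, do not present a lower cost per visit as an economic benefit unless cost per patient is shown with it.
4. State which facilities' costs are included. Data collection refers to the facilities taking part, which are primary care centres, and the article does not show that secondary or tertiary costs are captured. A per-patient figure limited to primary care must be labelled as such.

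Cost of the change: visits and costs are already extracted for consenting patients, so a per-patient figure for participating facilities should need little beyond rewording. The sponsor should confirm that the accounting source can be linked to individual patients' use of services and does not supply only facility averages. The per-patient result may look less favourable than the per-visit one, and wider coverage than participating facilities would need further data.
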